### Urinary PAC content

At the beginning of the trial, participants will be offered the option to provide a 24-h urine collect for targeted metabolomic characterization of PAC metabolites using ultra-high-performance liquid chromatography coupled to tandem mass spectrometry, performed by a chemist blinded to treatment allocation.

### Compliance and side effects

The cranberry extract capsules will be distributed at each visit and participants will be asked to bring remaining capsules the next visit in order to count remaining capsules. The participants will fill out a daily journal to record compliance, transient UTI symptoms and any adverse effects related to capsule intake. A bi-monthly email reminder will be sent to encourage participation. Each participant will receive an email reminder in the week preceding each visit. Evaluation of side effects will take place at each visit and participants will be asked to document symptoms (nausea, dyspepsia, abdominal pain, bloating and headaches) in their daily journal. In the presence of severe side effects, participants will be allowed to discontinue the intervention and remain in the study in order to preserve the intention to treat analyses.

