**Fig. 1 Fig1:**
[figure not shown]
Study procedures and characteristics of study visits

The primary objective is to evaluate, in sexually active women who present r-UTIs, the effects of a standardized cranberry extract containing 37 mg type-A linkage PACs per day, compared to a control dose of 2 mg PACs per day during a 6-month period on the incidence rate of newly symptomatic UTIs during a 6-month follow-up period. Secondary objectives are: (1) To evaluate the mean number of new symptomatic UTIs with pyuria as demonstrated by a positive leucocyte esterase test; (2) To detect the mean number of new symptomatic culture-confirmed UTIs; (3) To quantify urinary PACs metabolites in women who take a daily dose of 37 mg PACs per day compared to women who take a daily dose of 2 mg per day for 6 months; (4) To characterize women who present r-UTI based on known risk factors such as spermicidal contraception use, frequency of sexual relations, personal and familial history of UTI; (5) To describe the side effects of daily intake of cranberry extract containing 37 mg PACs compared to 2 mg PACs.

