### Study participants and recruitment

This clinical trial aims to enrol sexually active non-pregnant non-lactating women aged 18 years and over presenting culture-confirmed r-UTI (defined as ≥2 UTIs in the past 6 months or ≥ 3 UTIs in the past 12 months). Women will be recruited in the Laval University community in Quebec City, Canada, through list serves and local clinician referrals as well as posters in medical clinics, social media, paid advertising and word of mouth. Women wishing to participate will contact the study coordinator who will explain the research project to them and verify eligibility according to inclusion and exclusion criteria (Table 1). The risks and benefits of the study will be thoroughly discussed and the consent form will be signed at the first of three visits at the Institute on Nutrition and Functional Foods (INAF).

**Table 1 Tab1:** Admissibility criteria for the cranberry extract for prevention of recurrent urinary tract infections trial

Inclusion Criteria	
Sexually active healthy women	
Aged 18 years and older	
Recent history of recurrent urinary tract infections (UTIs)^a^	
≥ 2 UTIs in the past 6 months and/or	
≥ 3 UTIs in the past 12 months	
No consumption of cranberry juice, polyphenol or antioxidant supplements in the last 2 weeks	
Exclusion Criteria	
Pregnancy	
History of anatomical urogenital anomalies, urogenital tract surgery	
History of acute or chronic renal failure, nephrolithiasis	
History of intestinal diseases causing malabsorption	
Anticoagulant medication in the last month	
Known allergy or intolerance to cranberry	

^a^UTIs diagnosed by a clinician and treated with antibiotic therapy

Potential participants will need to restrain exposure to systemic antimicrobial agents or cranberry derivatives in the two weeks preceding enrolment. Women with anatomical abnormalities of the urinary tract, a history of renal disease (renal failure, nephrolithiasis) or intestinal disease causing malabsorption (Crohn’s disease, Celiac disease), or anticoagulant therapy will be excluded. Furthermore, we will exclude women with known allergy or intolerance to cranberries.

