#### Clinical follow-up

Each visit (0, 12 and 24 weeks) will include a short questionnaire documenting socio-demographic characteristics (*T* = 0 only), medication and natural health product intake, quality of life (SF-12) [23], risk factors for UTIs, and a validated food frequency questionnaire (FFQ) [24] modified for our study to specifically include foods containing PACs. Double data entry will be performed under the study coordinator supervision in order to promote data quality. Participants will be instructed to obtain a midstream urine sample according to standard methods suggested by the microbiological laboratory. A dipstick urinalysis using Chemstrip 9 (Roche Diagnostics USA) and a pregnancy test (ß-hCG) will be completed. Three 10 ml tubes will be placed in a − 80 °C freezer for urinary PAC metabolites measurements by ultra-high performance liquid chromatography coupled with mass spectrometry, and the urine sample for culture will be refrigerated and transported to the microbiology laboratory at the CHU de Quebec – Universite Laval within 24 h after collection.

During their participation, the women will be asked to contact the study coordinator if they present symptoms of UTI in order to schedule a visit at INAF to confirm the diagnosis by urinalysis and urine culture and to receive an appropriate antibiotic prescription based on their medical history and allergies. Women unable to present themselves at INAF will be prescribed antibiotics waiving a confirmation of their UTI. Women wishing to discontinue the consumption of capsules will be asked to present themselves at the 3 and 6-month visit in order to complete intention to treat analysis. The participants will be asked not to consume other products containing cranberry derivatives for the duration of the study and to consume their cranberry extracts 2–4 h preceding each visit. Participants will also be asked to limit intense physical activity for 24 h preceding each visit. After 24 weeks of participation, women will be provided with the option of prolonging their participation for an additional 24 weeks, with follow-up visits at 36 and 48 weeks. This data will provide information on seasonal variations in the incidence of UTI.

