#### Sample size and statistical analysis

Statistical analyses will be performed using SAS 9.2 (SAS Institute Inc., USA). All analyses will be based on the intention-to-treat principle before unmasking the treatment groups. The baseline characteristics of both groups will be compared using a Student’s t test for continuous variables and a generalized linear model for nominal variables. The Poisson regression model, which allows us to adjust for participants that were lost to follow up, will be used to compare the incidence of UTI during the 6-month follow up period as well as side effects of the treatment. Subgroup analyses will be performed in order to evaluate the impact of cranberry capsules in pre- and post-menopausal women as well as women with certain risk factors for complicated UTI such as pelvic floor disorders and diabetes.

Based on the literature [17], we estimate that 35% of patients in the control group will present at least one UTI during the 6-month follow-up period. In total, 126 women will need to be recruited in order to detect a clinically significant difference of 25% between the 2 groups (10% of women assigned to the experimental group will have at least 1 UTI with a power of 80%). Based on our past clinical trial experience [25], we estimate that 15% of randomized participants will be lost to follow up, therefore 148 women will need to be recruited in order to have at least 126 participants who will complete the 24-week intervention.

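### Outside five named symptoms, the daily journal asks only for adverse effects linked to the capsules, and the visit evaluation is not said to be free of attribution, so the side-effect comparison can under-record events

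*Protocol article*

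**What the plan says.** All references are to the protocol article.

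- **Safety objective** (Study design and objectives, secondary objective 5): "To describe the side effects of daily intake of cranberry extract containing 37 mg PACs compared to 2 mg PACs".
- **Analysis** (Sample size and statistical analysis): the Poisson model "will be used to compare the incidence of UTI during the 6-month follow up period as well as side effects of the treatment". The objective is worded as descriptive, but a between-arm comparison is planned.
- **Journal, general rule** (Compliance and side effects): "The participants will fill out a daily journal to record compliance, transient UTI symptoms and any adverse effects related to capsule intake". The words that set the condition are "any adverse effects related to capsule intake".
- **Journal, named symptoms, and visits** (same section): "Evaluation of side effects will take place at each visit and participants will be asked to document symptoms (nausea, dyspepsia, abdominal pain, bloating and headaches". The list closes there and refers to the daily journal. The five symptoms carry no relatedness condition.
- **Visit timing** (Clinical follow-up): visits are at 0, 12 and 24 weeks. The questionnaire content given there covers medication and natural health products, quality of life, UTI risk factors and diet. It names no general adverse-event question.
- **Blinding** (Study randomization): clinical investigation, data collection and assessment are blinded to allocation.

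**The concern.** In a randomised double-blind trial, the contrast between arms tells us whether the higher dose causes more events. That works best when events are collected whatever their suspected cause and relatedness is judged separately. Here the journal wording puts the causal judgement first for everything outside the five named symptoms. The participant fills in the journal, so in practice the judgement is hers, although the article does not say so explicitly. An event that is never written down cannot be restored by any later analysis.

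The visit evaluation is a second route into the record, but it too is worded as an evaluation of side effects, a term that itself suggests attribution. With 12 weeks between visits, the journal is the only day-to-day record described. At stake is how far a finding of no difference in side effects between 37 mg and 2 mg can be relied on for events outside the list.

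**Working it through.** The article gives no side-effect rate, capture fraction or safety power, so there is no stated figure to reproduce. The check is first a reading of the text and then an illustration on assumed values.

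**1. What each route captures.**

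| Route | Five named symptoms | Any other event |
|---|---|---|
| Daily journal | Recorded, no relatedness condition | Recorded if judged related to the capsules |
| Visit evaluation | Not restricted by the text | Not restricted by the text, but not said to be free of attribution |

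The attribution condition is explicit for the journal. For visits, the article leaves the matter open.

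**2. Equal under-capture: effect on the Poisson rate ratio.** Let a fraction c of unlisted events be recorded in both arms.

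- Observed ratio = (c × rate at 37 mg) / (c × rate at 2 mg) = true ratio. It does not change.
- Standard error of the log ratio ≈ √(1/d₁ + 1/d₂), where d₁ and d₂ are the recorded events. Both scale with c, so the standard error is multiplied by 1/√c.

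Inputs: 148 women at 1:1 gives 74 per arm (document). Event risks of 10% versus 4% and c between 30% and 70% are assumptions. Full capture gives 74 × 0.10 = 7.4 and 74 × 0.04 = 2.96 events, a ratio of 2.5.

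| c | Expected events | Risk difference (points) | SE of log ratio | Approx. 95% interval for the ratio of 2.5 | 1/√c |
|---|---|---|---|---|---|
| 100% | 7.4 vs 2.96 | 6.0 | 0.688 | 0.65 to 9.6 | 1.00 |
| 70% | 5.18 vs 2.07 | 4.2 | 0.822 | 0.50 to 12.5 | 1.20 |
| 50% | 3.70 vs 1.48 | 3.0 | 0.973 | 0.37 to 16.8 | 1.41 |
| 30% | 2.22 vs 0.89 | 1.8 | 1.256 | 0.21 to 29.3 | 1.83 |

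For example, at full capture √(1/7.4 + 1/2.96) = 0.688 and exp(ln 2.5 ± 1.96 × 0.688) = 0.65 to 9.6. The interval includes 1 even with complete recording.

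**3. A commoner event, on proportions.** Assumed true risks are 25% versus 10%, with 74 per arm and two-sided 5%. Power = Φ{[(p₁ − p₂) − 1.96√(2p̄(1 − p̄)/74)] / √[(p₁(1 − p₁) + p₂(1 − p₂))/74]}, with p₁ and p₂ each multiplied by c and p̄ their mean. Results: 67% at full capture, 53% at 75%, 36% at 50% and 20% at 25%.

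**4. Chance of seeing a rare event at all.** For an assumed 2% event, P(at least one recorded case in an arm of 74) = 1 − (1 − 0.02c)⁷⁴. Results: 78% at full capture, 52% at 50% and 31% at 25%.

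**5. Unequal capture: possible bias.** If the fractions are c₁ (37 mg) and c₂ (2 mg), the observed ratio = true ratio × c₁/c₂. With both fractions anywhere in the assumed 30% to 70% range, the multiplier lies between 0.3/0.7 = 0.43 and 0.7/0.3 = 2.33. These are the extremes of an assumed range, not an expectation. They require attribution to differ by arm.

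**The case against.** The strongest reply is that the same section provides a side-effect evaluation at every visit, and nothing confines it to journal entries, the five symptoms or events the woman blames on the capsules. This is also a journal article. Visit checklists and adverse-event definitions normally sit in a fuller document, and their absence here is no fault. That reply stands against any statement that unlisted events enter the record only by participant attribution, or that they are certainly missed. It does not remove the point, because the journal condition is a collection rule that the article itself states.

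A reader might also infer that the exclusions identify harms the trial ought to prompt for, such as bleeding from "Anticoagulant medication in the last month", or stones and allergic reactions from the other criteria. The documents do not support this. Table 1 gives no safety rationale for any exclusion, and it also lists conditions such as urogenital anomalies and malabsorption that need not signal an expected harm. Abdominal pain is already a named symptom, and hematuria is assessed as a urinary symptom. No prompt list follows from the exclusions.

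A reader might further infer that the filter makes the higher dose look safer than it is. That is not shown either. Equal under-capture leaves the rate ratio alone. If women's beliefs followed their true allocation, and those who believed they had the high dose attributed more, the higher dose would look worse. Blinding limits this route. It is not closed by the text: opaque packaging is described as hiding colour differences from the research team, and allocation guesses are to be documented at the last visit. Belief-driven bias is therefore possible but not demonstrated.

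**Conclusion.** The point holds as a minor weakness on a secondary objective. For events outside the five named symptoms, the journal makes recording depend on attribution, and the article does not say that the visit evaluation collects events regardless of cause. The between-arm comparison can therefore under-record unlisted events and lose precision. It could be biased in either direction if attribution differs between arms.

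The size is unknown. The precision figures rest on assumed event rates and capture fractions and on equal capture in both arms. They show how loss of recording would act, not that events are being lost. In the 10% versus 4% example, the comparison is inconclusive even with full capture, so the filter makes an already imprecise comparison weaker rather than turning a clear result into a false one.

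**What to change.** In Compliance and side effects, state that the journal and each visit record all adverse events whatever the suspected cause, with relatedness to the capsules as a separate item. In the analysis section, state that all events are compared by arm first and the related subset second. If the visit evaluation already collects events regardless of attribution, saying so would settle that half of the point.

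The Trial status section reports recruitment complete in March 2017 and follow-up visits continuing into Winter 2018, so a change would reach only the remaining follow-up. Journal data collected under the current wording should be labelled as participant-attributed when reported.

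The cost is a revised journal page and visit form, with no extra visits, tests or participants. There will be more unrelated events to record and tabulate. A change during follow-up leaves two collection methods in one trial, so the two periods should be kept distinguishable in the tables.

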### Blinding and contamination Bias

The proportion of women who will guess their group allocation correctly will be documented with a short questionnaire at the last visit. To control for contamination bias, any antibiotic therapy during the study period will be declared to the study coordinator and PAC consumption will be measured by FFQ for the 24 h preceding each visit.

## Discussion

Use of cranberry derived products in the prevention of r-UTI remains controversial, with no definitive evidence to show superiority of the cranberry compared to antibiotic therapy [17, 18]. There is some evidence that cranberry products may reduce the incidence of UTIs compared to placebo, though the most effective amount and concentration of PACs that must be consumed and the duration for the intervention are unknown [17]. To our knowledge, this study is the first large, prospective randomized clinical trial assessing the impact of a cranberry extract capsule standardized to 37 mg PAC per day compared to 2 mg PAC per day in preventing UTIs in healthy women presenting r-UTI.

Incidence of symptomatic UTI during the 6-month follow-up period was selected as the primary end-point in this trial because it is the most important, clinically relevant long-term outcome for patients. We used three classifications for UTI analyses: symptomatic UTI, dipstick-positive UTI and culture-confirmed UTI. Symptomatic UTI was diagnosed if a participant presented at least one of the following symptoms: dysuria, pollakiuria, urinary urgency, suprapubic pain or hematuria. In the presence of clinical symptoms, participants will be asked to provide a urine sample in order to perform a dipstick test and a urine culture. Positive leucocytes or nitrites will indicate a positive dipstick test [26]. A positive urine culture will be designated by greater than 10^6^ colony-forming units, according to the microbiological laboratory standards of the CHUL hospital. In our study, antibiotics will be prescribed in the presence of clinical symptoms in combination with either a positive urine dipstick test and/or positive urine culture.

### Implications of findings

Many Canadian women who present r-UTI commonly use over the counter cranberries-derived products with inadequate labelling of PACs concentrations. For cranberry products with quantification of PACs, these concentrations rarely exceed 2 mg in Canada [21]. Various trials have tested the effectiveness of cranberry derived products, essentially in juice form, and their results remain discordant mainly due to the lack of standardization and low doses of PACs in tested products. Hence, the intrinsic activity of cranberry PACs, demonstrated against *Escherichia coli* in vitro, has never been optimized for the prevention of UTI. The results generated from this trial will clarify the role of cranberry extracts standardized in PACs on the decreased incidence of UTI in women presenting r-UTIs, will evaluate the differences in the incidence of UTI on the basis of different PACs concentrations and will respond to the recommendations reported in the last Cochrane meta-analysis [17].

This report provides comprehensive methods for a clinical trial on the prevention of RUTI by cranberry extract capsule intake. The strengths of this trial include the quantification and standardisation of PACs contained in the cranberry extract capsule and a randomized, double blind, controlled trial method. Our trial will add to a growing body of literature regarding cranberry extract capsule for the prevention of r-UTI in healthy women. In addition, the data set and specimen bank generated from conducting this trial will enable researchers to understand the metabolites of type-A PACs produced after prolonged consumption of cranberry capsules.

## Trial status

Participant recruitment started on August 18th 2015 and was completed in March 2017. Study follow up visits will continue into Winter 2018.

## Abbreviations

FFQ: Food frequency questionnaire
PAC: Proanthocyanidin
RCT: Randomized controlled trial
r-UTI: Recurrent UTI
UTI: Urinary tract infection
